## Abstract

**Background:**

To improve immunization coverage, most interventions that are part of the national immunization program in India address supply-side challenges. But, there is growing evidence that addressing demand-side factors can potentially contribute to improvement in childhood vaccination coverage in low- and middle-income countries. Participatory engagement of communities can address demand-side barriers while also mobilizing the community to advocate for better service delivery. The objective of this study is to evaluate the impact of a novel community engagement approach in improving immunization coverage. In our proposed intervention, we go a step beyond merely engaging the community and strive towards increasing ‘ownership’ by the communities.

**Methods/Design:**

We adopt a cluster randomized design with two groups to evaluate the intervention in Assam, a state in the northeast region of India. To recruit villages and participants at baseline, we used a two-stage stratified random sampling method. We stratified villages; our unit of randomization, based on census data and randomly selected villages from each of the four strata. At the second-stage, we selected random sub-sample of eligible households (having children in the age group of 6–23 months) from each selected village. The study uses a repeated cross sectional design where we track the same sampled villages but draw independent random samples of households at baseline and endline. Total number of villages required for the study is 180 with 15 eligible HHs from each village. Post-baseline survey, we adopt a stratified randomization strategy to achieve better balance in intervention and control groups, leveraging information from the extensive baseline survey.

**Discussion:**

The proposed intervention can help identify barriers to vaccination at the local level and potentially lead to more sustainable solutions over the long term. Our sampling design, sample size calculation, and randomization strategy address internal validity of our evaluation design. We believe that it would allow us to causally relate any observed changes in immunization coverage to the intervention.

**Trial registration:**

The trial has been registered on 7th February, 2017 under the Clinical Trials Registry- India (CTRI), hosted at the ICMR’s National Institute of Medical Statistics, having registration number CTRI/2017/02/007792. This is the original study protocol.

## Background

Immunization is a globally accepted public health intervention that helps avert vaccine-preventable diseases. Incomplete- and non-immunization increases the risk of illness and death among children. The Global Vaccine Action Plan (GVAP 2011–2020) sets the goal of 90% coverage at the national level and 80% in every district or equivalent administrative unit with all vaccines in national programs by 2020 [1]. India is one of the 194 Member States of the World Health Assembly which endorsed the GVAP framework in 2012. Despite a long standing national program for immunization in India since 1985, only 65.2% of 12–23 month old children are fully immunized (RSOC, 2013–14) [2]. Full immunization is defined as children receiving one dose of Bacillus Calmette–Guérin (BCG) vaccine to prevent tuberculosis, three doses of oral polio vaccine (OPV3), three doses of diphtheria-pertussis-tetanus vaccine (DPT3) or the more recently introduced Pentavalent (DPT-Hepatitis B-Haemophilus Influenzae type B) vaccine, and one dose of measles vaccine. Completion of schedule of vaccines that require multiple doses (e.g., OPV and DPT or Pentavalent) remains a major challenge towards achieving higher full immunization coverage (FIC). Both demand- and supply-side bottlenecks contribute to sub-optimal vaccination coverage rates in India [3–8].

In the context of universal immunization program (UIP) in India, most of the existing interventions are geared towards addressing supply-side challenges such as ensuring better immunization services and more focused implementation by deploying more health workers across health facilities, introducing alternate vaccine delivery system, including new vaccines in the immunization schedule, organizing sessions in hard-to-reach areas, and initiating supplementary immunization activities for children who are missed out in the routine immunization program [5, 9, 10]. But there is a growing body of literature showing that demand-side interventions lead to significant improvement in childhood vaccination coverage in low- and middle-income countries [11, 12]. Community engagement approaches can address demand-side barriers while also mobilizing the community to advocate for better service delivery [13, 14]. With the growing realization that community-level factors influence vaccination uptake, more recent strategies to increase vaccination coverage have attempted to focus on community-based interventions [15–18].

Existing community engagement programs, however, mostly focus on communication activities that do not actively involve communities in the planning, monitoring and surveillance activities [15]. Participatory engagement of communities can help identify barriers to vaccination at the local level and thus might lead to sustainable solutions in a manner which a top-down approach cannot achieve. Our proposed intervention goes a step beyond merely engaging with communities and strives towards increasing a sense of community ‘ownership’.

In various steps of the proposed intervention, referred to by the acronym SALT (Stimulate, Appreciate, Learn, Transfer), the communities lead the way — they identify the challenges, they take actions based on where they are and what they want to achieve, learn from their actions and share their experience with other communities. Trained facilitators stimulate the communities to leverage their own strengths to address their concerns, and accompany them through a systematic process of learning from action.

This community-based approach has been shown to be effective in generating behaviour change in other contexts. The WHO-UNICEF evaluation of AIDS Competence Process (ACP) in Papua New Guinea (2009) concludes that ACP is an effective approach in combating HIV/AIDS through local empowerment [19]. Economic evaluation of ACP in Thailand (2011) shows that it is likely to be cost-effective when comparing incremental cost-effectiveness ratio of the ACP with other HIV prevention programs [20]. In the context of malaria, a retrospective study of SALT versus non-SALT districts in Togo shows significant increase in impregnated bednet use and decrease in malaria prevalence among children under five [21]. A recent study (unpublished) in Democratic Republic of the Congo found that SALT intervention can reduce resistance to vaccination and increase vaccination rates for oral polio vaccine [22]. However, the evaluation design and method used in the study did not measure the attributable impact of SALT.

In the last 5–6 years, according to the different health and demographic surveys, there has been no significant improvement in the FIC in India [2, 4, 23]. It has been suggested that approaches in which communities play a prominent role may be effective for improving immunisation coverage [15]. We aim to assess the impact of this novel community engagement approach (SALT) in increasing immunization coverage. The objective of this impact evaluation study is to generate high quality evidence that will allow us to causally attribute the changes in immunisation coverage, if any, to the SALT intervention.

## Methods/Design

### Study setting

The study site is in Assam, a north-eastern state of India. Historically, Assam is known to have poor public health indicators and weak health infrastructure [24]. Full immunization coverage in Assam (55.3%) is lower than the national level (65.2%). Dropout rates for vaccines that require multiple doses are higher in Assam than the national figures [2]. According to the latest SRS bulletin (2015) [25], Assam has the second highest infant mortality rate in the country, 47 deaths in infants less than a year old per 1000 live births, which exceeds the national average of 37. We considered 3 districts from Assam- Bongaigaon, Kamrup rural, and Udalguri. Figure 1 shows the location of Assam on India map and the three selected districts on a map of Assam.

**Fig. 1 Fig1:**
[figure not shown]
Location of Assam on India map (inset) and three selected districts- Bongaigaon, Kamrup (rural) and Udalguri- on Assam map. Source: https://www.mapsofindia.com/maps/assam/

Stratified purposeful sampling was used so that the selected districts represent varied socio-demographic characteristics of Assam. Table 1 illustrates the variation across the three districts in terms of selected indicators. We considered only rural areas of selected districts for this impact evaluation study.

**Table 1 Tab1:** Socio-demographic characteristics (census 2011) of three selected districts of Assam along with DPT3 coverage rate (DLHS-3, 2007–08)

District	Population	Urban (%)	Tribal (%)	Female literacy rate	Muslim (%)	DPT3 coverage
Bongaigaon	7,38,804	14.9	2.5	64.4	50.2	56.2
Kamrup rural	15,17,542	9.4	12.0	69.5	39.7	67.2
Udalguri	8,31,668	4.5	32.1	58.0	12.7	62.0

### Study design

We adopted a cluster randomized controlled trial (cRCT) design with two groups to evaluate the intervention. The intervention group receives SALT intervention for about a year (March 2017–March 2018) along with the routine immunization (RI) services. The control group received RI services alone. Cluster randomized design is appropriate here as opposed to individual or household level randomization as the intervention is intended for implementation at the community (village) level, the village being our unit of randomization.

The study uses a repeated cross sectional design where we track the same sampled villages but draw independent random samples of households (HHs) at baseline and endline. Post intervention, for the endline survey we do not plan to follow up the same HHs unlike most other RCTs, as estimating immunization coverage rates requires targeting a particular age-group of children. The children sampled at baseline would have mostly grown beyond the desirable age limit by the time the endline survey is due. The HHs in the baseline may no longer satisfy the eligibility criteria (having children in that particular age group) at the time of the endline survey – although there may be some overlap.

### Sampling strategy: Recruitment of clusters and participants

Within each district, we considered a two-stage cluster sampling design. In the *first stage*, we selected villages using a stratified sampling technique. We stratified villages, within a district into four strata and then randomly selected villages from each stratum. For the selection of villages, we used census 2011 village-level data as our sampling frame. The following villages were excluded from the census sampling frame: 1) villages having less than 50 HHs as getting enough number of eligible HHs–having children in the age group 6 to 23 months- would be a challenge and 2) villages having more than 500 HHs as there would be logistical challenges to get the community together for implementation within the timeframe and resources of the study. To stratify the villages, we used the following village-level indicators: population size, percentage of Scheduled Caste (SC), percentage of Scheduled Tribe (ST), and female literacy rate. SCs and STs are various officially designated groups, recognized in the constitution of India, of historically disadvantaged people [26]. Based on these indicators we developed a composite index that was then used to construct the four strata based on the quartiles of the index. Twenty villages were selected from each of the four strata using simple random sampling method. The choice of stratified sampling design ensures a representative sample of villages, having varied socio-demographic characteristics, within each district. The requirement of 20 villages per stratum stems from the sample size calculation, as discussed in the section on Sample Size. This led to 80 villages (20 × 4) in each district, resulting in total 240 villages across 3 districts of Assam for the baseline survey.

In the *second stage*, from all sampled villages, after houselisting a random sample of 15 eligible HHs was selected for the baseline survey. In a selected household, all mothers having children in the age group 6–23 months were eligible to participate in the survey. From mothers, we collected information pertaining to her youngest 6–23 month old child. The flowchart in Fig. 2 provides a visual display of the sampling strategy (in blue). In the endline survey, while the sampled villages will remain the same, a new random sample of 15 eligible HHs will be drawn from each village. The baseline survey was done during June–August, 2016 and the endline survey is planned to be conducted after the conclusion of the intervention, during June–August 2018.

**Fig. 2 Fig2:**
[figure not shown]
Flow chart describing sampling strategy and randomization plan for the cluster randomized controlled trial within a district: Exact same flow chart is applicable for all three districts

### The intervention

This community engagement intervention originated at the Constellation [27], a NGO registered in Belgium. We refer to the intervention by the acronym SALT: stimulate, appreciate, learn, and transfer. The intervention starts with home visits by trained facilitators to villages. Facilitators engage with people, listen to the hopes and concerns of people, appreciate their strengths, and eventually bring the community together to discuss the common values they share. SALT home visits are a crucial starting point as it helps to build trust between the facilitators and the community and to identify strengths available in the community. The next step is collective dream building which starts from individuals and small groups and then involves the wider community. In our context, this is the dream of healthy children in the community and immunization is a component that can contribute to healthy children.

Once the community embraces its dream, a self-assessment exercise starts under the guidance of the facilitator, in order to understand where the community stands today with respect to practices linked to their shared dream. It is important to note that the practices must ideally come from the community. The facilitators stimulate the conversation so that immunization related practices emerge during self-assessment. The self-assessment framework requires the community to assess itself on the set of practices defined by the community from level 1 to level 5 where level 1 indicates a low level of competence and level 5 indicates a high level of competence. The central idea behind the self-assessment exercise is that the community assesses themselves, rather than the facilitator assessing them. Thus this is not about an ‘expert’ coming from outside to assess the community and advise it of its weaknesses and its strengths.

In the next phase, the community chooses three priority practices, relevant to their shared dream, where it feels that it can make progress within a stated timeframe (say, 2–3 months). The discussion evolves around what actions need to be taken in order to reach a next desired level from the current level agreed by the community during self-assessment. For each selected practice, the community itself comes up with certain number of actions, based on its strengths and resources, which would help them reach the target level within the specified period of time. Often specific individuals or groups are identified from the community who take responsibility for each of the actions. To measure the effectiveness of action plan some indicators are defined by the community members.

This is followed by the action phase and the review process. The emphasis is that a plan is used to help take action, with actions taking precedence. Facilitators then bring communities together to share with and learn from each other in a ‘knowledge fair’ when transfer of knowledge and experience takes place between communities. Depending on the progress and timeline allotted for the intervention, the community might revisit the dream, and the various steps in the process. A pictorial illustration of SALT intervention and its processes are presented in Fig. 3.

**Fig. 3 Fig3:**
[figure not shown]
Pictorial illustration of different steps of SALT intervention

### Evaluation outcomes

Our study will assess the intervention’s impact on the following primary outcomes: FIC in children 12–23 months old and coverage rate of three doses of DPT/Pentavalent in 6–23 month old children. As secondary objectives we will study the impact of our intervention on dropout rates between different doses of DPT and OPV, timely immunization, and inequities in immunization coverage by gender, birth order, and various religious and caste groups. In addition, we will explore the intervention’s effect on common childhood illnesses such as diarrhea and acute lower respiratory infection. We will also measure other outcomes which fall on the causal pathway including awareness of immunization service provision in mothers, health service utilization (antenatal check-up and institutional delivery), perception of adherence and completion of immunization schedule in protecting children from diseases, beliefs regarding community engagement, action and practices in the context of child health, and community involvement and ownership.

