### Balancing checks

Balance between intervention and control groups was examined with respect to potentially important covariates after randomization of the 240 villages using baseline data. Although randomization happened at the village level, the unit of analysis is the child. Hence, we performed balancing checks at the level of village, child, child’s household and the mother. Balance was re-examined after excluding the villages discarded to minimize intervention-control contamination. Results in Table 3 suggest that reasonably good balance has been achieved across indicators for villages, children, their HHs, and mothers. This is expected as the randomization of villages to intervention and control groups happened within stratum, after stratifying the villages based on several of the indicators presented in Table 3. The two groups remain balanced after excluding intervention and control villages discarded to minimize intervention-control contamination.

**Table 3 Tab3:** Balancing checks based on selected village, household (HH), mother and child-level indicators: comparison between intervention and control groups

Characteristics	After randomization of all 240 baseline survey villages			After discarding villages to minimize contamination (180 villages)		
	Control	Intervention	*p*-value*	Control	Intervention	*p*-value*
Village-level indicators						
Village has subcentre	40.5	39.2	0.8334	39.8	41.7	0.7926
Village has secondary school	31.0	25	0.3034	29.6	26	0.5833
Village experienced flood last year	30.2	37.5	0.2359	31.6	35.4	0.5787
% of HHs in village living more than 50 years in same village	75.9	76.5	0.6841	77.2	76.1	0.8800
% of tribal HHs in village	26.4	26.2	0.5359	25.6	27.3	0.6494
% of mothers in village with education HS ^a^ or more	12.3	13.1	0.6777	12.6	13.6	0.6390
% of mothers in village receiving full antenatal care	41.9	42.1	0.936	42.5	43	0.8386
Household-level indicators						
Average HH size	5.33	5.28	0.4336	5.34	5.3	0.4867
Household head is Muslim	27.9	32.3	0.4104	27.7	30.2	0.6453
Household has (pour) flush toilet	35.9	33.6	0.5033	35.3	35.1	0.9965
Household belongs to poorest wealth quintile	19.7	19.7	0.9838	20.4	17.3	0.2405
Average time (in minutes) from household to vaccination site	19.9	20.6	0.5764	19.9	19.9	0.6037
Mother- and child-level indicators						
Mothers received full ANC when pregnant with child	41.9	41.9	0.9612	42.4	42.9	0.8787
Child was born in health facility	85.9	86.5	0.7941	84.9	88.4	0.2184

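### Institutional delivery, antenatal care and timeliness are outcomes with no birth-date limit, although for many endline children these events were over before SALT began

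*Protocol article*

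**What the plan says.** On timing, the Study design section states: "The intervention group receives SALT intervention for about a year (March 2017–March 2018"). The sampling section adds that "the endline survey is planned to be conducted after the conclusion of the intervention, during June–August 2018".

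On whom the data describe, the sampling section says: "From mothers, we collected information pertaining to her youngest 6–23 month old child".

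On outcomes, the Evaluation outcomes section names as primary "FIC in children 12–23 months old and coverage rate of three doses of DPT/Pentavalent in 6–23 month old children". Timely immunization and dropout between DPT and OPV doses are secondary. The section then says: "We will also measure other outcomes which fall on the causal pathway including awareness of immunization service provision in mothers, health service utilization". In full, that last item reads "health service utilization (antenatal check-up and institutional delivery"). It sets no limit on date of birth or conception.

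The balance table shows how these items are recorded. They belong to the index child: one row reads "Mothers received full ANC when pregnant with child", and another gives whether that child was born in a facility.

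**The concern.** An outcome can lie on the causal pathway only if it happens after the intervention has begun. The index delivery and index pregnancy are dated events that cannot be revised later. In a child born before March 2017 both were over before SALT existed in the village. Such children add the same expected value to both arms and pull the difference toward zero.

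The Discussion wants to be able to tell an ineffective SALT from a poorly implemented one if no impact is seen. A flat result for delivery or antenatal care would look like evidence that SALT failed to move these steps. Part of that flatness would come only from the calendar. The same applies to the timeliness of any dose that fell due before SALT started.

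**Working it through.** **Inputs.** SALT start: March 2017, taken as 1 March and then as 31 March (Study design). Endline: 1 June to 31 August 2018, midpoint 16 July (sampling section). Age band: 6 to under 24 months, 18 months wide. Assumptions not in the document: ages uniform across the band, a 9-month pregnancy, and a third DPT dose due at 14 weeks (98 days, 3.2 months). Taking the mother's youngest eligible child shifts ages slightly younger and lowers the shares a little.

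**Formulas.** Let *T* be the months from SALT start to interview (15.0, 16.5 and 18.0 for a 1 March start).
- Born before the start: (24 − *T*)/18
- Pregnancy wholly after the start: (*T* − 9 − 6)/18
- Third DPT dose due before the start: (24 − *T* − 3.2)/18

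| Interview date | Born before SALT | Pregnancy wholly after start | Third DPT dose due before SALT |
|---|---|---|---|
| 1 June 2018 | 9.0/18 = 50% | 0/18 = 0% | 32% |
| 16 July 2018 | 7.5/18 = 42% | 1.5/18 = 8% | 24% |
| 31 August 2018 | 6.0/18 = 33% | 3.0/18 = 17% | 15% |

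With a 31 March start the columns become 55/47/39%, 0/3/11% and 38/29/21%. On either start date, pregnancies that straddle it make up much of the remainder: with a 1 March start, 9/18 = 50% at each interview date.

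**Delivery.** If SALT changes institutional delivery by *d* points in births after its start, the unrestricted comparison estimates *d* × (1 − 0.42) = 0.58*d* at mid-survey (0.50*d* to 0.67*d*). This treats every birth after the start as fully exposed, so it understates the attenuation.

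**Precision after restriction.** At mid-survey about 15 × 0.583 = 8.75 children per village remain. The contrast grows by 1/0.583 = 1.71. The document gives no intracluster correlation (ICC) for delivery, so I show a range. If it is 0, the standard error grows by √(15/8.75) = 1.31. If it equals the 0.17 given for DPT3, the effective number per arm goes from 90 × 15/(1 + 14 × 0.17) = 399 to 90 × 8.75/(1 + 7.75 × 0.17) = 340, and the standard error grows by √(399/340) = 1.08. The gain in contrast is larger than the loss of precision in both cases.

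**DPT3 coverage.** The plan's own figure first. For 84% vs 92%, two-sided 5% and 80% power, *n* = 7.849 × (0.84 × 0.16 + 0.92 × 0.08)/0.08² = 255. Then 255.1 × 3.38/15 = 57.5 villages per group, against the stated 57, so it is reproduced. At 90 villages per group the power for 8 points is 94%.

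Now suppose, as an extreme, that no child past 14 weeks at SALT start could respond. The average difference becomes 8 × (1 − 0.15) = 6.8 to 8 × (1 − 0.32) = 5.4 points, and power is about 83% down to about 62%. This bounds the loss under the 14-week assumption and a 1 March start. It is not an estimate, because it allows no catch-up at all. The oldest endline children were only about 6–9 months old on 1 March 2017 (24 − *T*; at most about 10 months with the later start), and any who lacked a dose had the whole SALT year to receive it.

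**The case against.** Two objections deserve weight.

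*Delivery and antenatal care are minor outcomes.* They are neither primary nor secondary, the article fixes no test for them, and a fuller analysis plan may define their population. A process evaluation is also planned to help interpret a null result. This limits the consequence: the primary conclusion is not directly touched. It does not remove the point, because the article places these events on the causal pathway and its own dates show that for a third to a half of the children they cannot be there.

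*The primary DPT3 outcome is not shown to suffer.* A reader might infer from the same dates that DPT3 is heavily diluted, or that an 8-point average would need an effect near the 16-point ceiling above 84%. The document does not support that. DPT3 is coverage at survey, and timeliness is a separate secondary objective. SALT can raise coverage only in children who would otherwise lack a dose at survey. Those children lacked it throughout the SALT year and were exposed to SALT in that state. A child already complete before SALT is part of the 84%. Even with no catch-up, 24% non-responders would imply 8/0.76 = 10.5 points in the rest, well short of 16. Assuming a lag before the community action phase would worsen these figures, but the article dates no such lag. This objection stands in full.

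**Conclusion.** The point holds for institutional delivery, antenatal care and timeliness. About 42% (33–50%) of endline children aged 6–23 months were born before a 1 March 2017 start, and about 8% (0–17%) of index pregnancies lie wholly after it. The unrestricted delivery effect would be at most roughly half to two thirds of the effect in births after the start. Antenatal care is affected more widely, since nearly all index pregnancies began before SALT. For timeliness, 15–32% of children had the third DPT dose due before the start. That share rests on the assumed 14-week due age and would be somewhat lower if timeliness allows a grace period.

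The birth and pregnancy shares rest on uniform ages and a 9-month pregnancy. A later start in March raises the share born before SALT.

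For DPT3 coverage, some dilution is possible, but its size cannot be derived from the document. The power range of about 83% to 62% is only a no-catch-up bound and does not show that the primary analysis is underpowered.

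**What to change.** Specify the following, by the child's date of birth and identically in both arms:

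- **Institutional delivery:** analyse births on or after the date SALT started. No upper limit is needed, because a child aged 6 months on 31 August 2018 was born around the end of February 2018, within the SALT year.
- **Antenatal care:** analyse pregnancies with a minimum overlap of *k* months with SALT, with *k* fixed before endline data are seen. The share kept is (*T* − *k* − 6)/18. At mid-survey this is 58% for any overlap, 42% for 3 months, 25% for 6 months and 8% for a whole 9-month pregnancy.
- **Timeliness:** analyse doses that fell due within the intervention period, with both a start and an end limit. On the 14-week assumption and an end date of 31 March 2018, 0–12% of children (4% at mid-survey) had the third DPT dose due after SALT ended.
- **Primary outcomes:** keep FIC at 12–23 months and DPT3 at 6–23 months as they are. At most, add one supporting DPT3 analysis by birth date relative to SALT start.

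The cost is wording, provided dates of birth are recorded, plus fewer children in the restricted analyses: about 50–67% of the sample for delivery, and fewer for antenatal care as *k* rises. Date of birth should not depend on allocation for children conceived before SALT, so the restriction keeps the randomized comparison for nearly all of the sample.
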